### Research objective and hypothesis

Although the American Diabetes Association (ADA) recommends at least 150 min/week of moderate-intensity aerobic physical activity or at least 90 min/week of vigorous aerobic exercise distributed over at least 3 days/week and with no more than 2 days consecutively without physical activity [28], a dose- response relationship with health benefits remains unclear. Therefore, the present study aims to evaluate the dosimetry of aerobic training programs in the regulation of oxygen kinetics, oxidative stress, cardiac autonomic function, and cardiometabolic parameters in T2DM. We hypothesize that varying the volume and intensity of aerobic training will result in a significant difference in oxygen uptake, oxidative stress, and cardiac autonomic function in patients with diabetes mellitus.

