#### Sample size calculation

The number of subjects was determined using Software G. Power 3.192. An effect size of 0.44 was obtained from the data relative to changes in maximum aerobic capacity in a study by Lambers et al. [38], which examined the effects of aerobic training on obesity and cardiovascular risk in T2DM. A priori analysis of sample size using the *F* test (repeated measures analysis of variance (ANOVA), within-between interaction) showed that the total sample size required would be 52 to have 95% power at effect size of 0.44 and alpha level of 0.05. Considering the dropout rate from a previous similar investigation [30], the total sample size obtained is 60 or 15 subjects per group, using the allocation ratio of 1 for the four groups.

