#### Statistical analyses

The intention-to-treat (ITT) analysis set will include all subjects who were randomized to the study and received at least one session of training. The normality of distribution will be examined for all variables and those found to have a non-normal distribution will be log transformed for further analyses. One-way ANOVA will be used to compare the groups at baseline. To test for the differences between groups and across two assessments, 4 × 2 split-plot ANOVA with group (LILV, LIHV, HIHV, control), time (baseline, 12 weeks) and interaction effect (Group × Time) will be employed. If the main effect of a group is found to be significant, the Bonferroni test will be employed as post hoc analysis. The significance level will be set at *p* < 0.05.

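### The hypothesis is about training dose, but the planned test and its 95% power belong to a four-arm comparison that includes the untrained control; the volume and intensity contrasts are neither named nor powered

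*Protocol article*

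**What the plan says.** Under Research objective and hypothesis, the article expects that "varying the volume and intensity of aerobic training will result in a significant difference in oxygen uptake, oxidative stress, and cardiac autonomic function". The Interventions section builds arms that separate the two components. LILV and LIHV train at the same intensity (50% VO2R) at 3 and 5 sessions a week. LIHV and HIHV both train 5 times a week, at 50% and 80% VO2R. The fourth arm has no supervised exercise.

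Statistical analyses specifies a 4 × 2 "split-plot ANOVA with group (LILV, LIHV, HIHV, control), time (baseline, 12 weeks) and interaction effect". The follow-up rule is: "If the main effect of a group is found to be significant, the Bonferroni test will be employed as post hoc analysis". The level is 0.05.

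Sample size calculation names the powered effect as the "within-between interaction" and reports that "the total sample size required would be 52 to have 95% power at effect size of 0.44 and alpha level of 0.05". On the source of that effect size it says: "An effect size of 0.44 was obtained from the data relative to changes in maximum aerobic capacity". No effect size is given for volume or for intensity.

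**The concern.** A 3-df test over four arms rejects when any arm differs from any other. The Abstract already treats a benefit of aerobic training as reported and the effect of dose as unknown, so a rejection driven by the control arm leaves the trial's own question open. The comparisons that would answer it are reached only through a post hoc step, and its trigger is the group main effect. That effect averages baseline and 12 weeks; it is not the interaction that was powered.

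Two misreadings are at stake. A significant four-arm result could be reported as support for the dose hypothesis. A non-significant volume or intensity comparison could be read as showing that dose does not matter, with the 95% figure cited in support, when the trial may not have been able to tell.

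**Working it through.** **Inputs.** From Sample size calculation: f = 0.44, alpha 0.05, power 95%, N = 52 (13 per arm) before dropout, 60 (15 per arm) randomised. From Statistical analyses: k = 4 groups, m = 2 assessments. Assumed, because the article does not give them: the pre-post correlation ρ, the pattern of arm means, and six Bonferroni pairs (all pairs among four arms, so 0.05/6 = 0.0083 each).

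**1. The plan's own figure.** For the within-between interaction, λ = f²·N·m/(1−ρ), df1 = 3, df2 = N − 4. With ρ = 0 and N = 52, λ = 0.1936 × 52 × 2 = 20.13 and power is 0.964. At N = 48 power is 0.948, so 52 is the smallest multiple of four that reaches 95%. At N = 60, λ = 23.23 and power is 0.984. With ρ = 0.5 the same formula would need only 28, so the stated 52 matches ρ = 0.

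**2. No dose effect at all.** Put the whole of f = 0.44 into control versus three equal training arms (pattern 0, 1, 1, 1). λ is unchanged, so the four-arm interaction rejects with probability 0.964 (N = 52) or 0.984 (N = 60), although both dose differences are exactly zero.

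**3. Power of each dose contrast.** In units of the SD of change, the spread of arm means is f_c = √(f²·2/(1−ρ)): 0.622 at ρ = 0 and 0.880 at ρ = 0.5. Dividing by the SD of the assumed pattern and multiplying by the step gives d. For example, the pattern 0, 1, 2, 3 has SD 1.118, so d = 0.622/1.118 = 0.557. Power is from the noncentral t with noncentrality d/√(2/n) and 4n − 4 df. The two-sided critical value at n = 13 is 2.752 for alpha 0.0083 and 2.314 for alpha 0.025.

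| Pattern (control, LILV, LIHV, HIHV) | ρ | d | Six-pair Bonferroni, n = 13 / 15 |
|---|---|---|---|
| 0, 2, 2.5, 3 (modest steps) | 0 | 0.27 | 2.5% / 2.8% |
| 0, 1, 2, 3 (equal steps) | 0 | 0.557 | 10% / 12% |
| 0, 1, 2, 3 (equal steps) | 0.5 | 0.787 | 24% / 29% |
| 0, 0, 1, 1 (all in volume) | 0 | 1.245 | 66% / 75% |
| 0, 0, 0, 1 (all in intensity) | 0 | 1.44 | 81% / 88% |

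For equal steps at ρ = 0, two contrasts at 0.025 each would have 20% / 23%.

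**4. Difference detectable with 80% power (SD of change), n = 13 / 15.** Six-pair Bonferroni: 1.42 / 1.31. Two contrasts at 0.025: 1.24 / 1.15.

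**5. The gate.** These are ungated tests on change scores. If the pairwise tests are made on change, requiring a significant group main effect first can only lower the figures. With no baseline difference, the main effect sees half of each change. At ρ = 0 it has the same power as the interaction (0.964 / 0.984). At ρ = 0.5 its λ is one third of the interaction's, and its power is 0.852 / 0.906, against more than 0.999 for the interaction.

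**The case against.** A reader might infer that the dose hypothesis will be declared confirmed by training versus control alone. The article does not say so. It never states that a significant four-arm test settles the hypothesis, and its post hoc tests would normally include both dose pairs. In the 0, 1, 1, 1 scenario with six pairs, the three pairs among trained arms are each tested at 0.0083, so the chance of declaring any dose difference is at most 3 × 0.0083 = 2.5%. The 96% is a correct rejection of equality across four arms, not a false dose claim. This stands: the omnibus can mislead, but need not.

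A reader might also infer that the dose contrasts have almost no power. That depends on a pattern and a correlation that the article does not give, and on a count of six pairs that it does not state. If the whole effect lies in one dose step, power is substantial.

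Keeping a control arm is also defensible. The Discussion seeks a threshold dose that brings about change, and this needs training-versus-control comparisons. The Abstract calls the aim exploratory, and a fuller plan might list contrasts. These points argue for keeping the control comparisons and against treating the matter as fatal. They do not remove the mismatch, because the model, the post hoc trigger and the power statement are all fixed in the article.

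**Conclusion.** The point holds as a mismatch between question, test and power. The four-arm result can be significant through training versus control alone (96% at N = 52, 98% at N = 60, if f = 0.44 lies wholly there and ρ = 0). The stated 95% does not describe the volume or intensity contrasts. Their power ranges from about 2.5% to 88% across the cases tabulated. Under six-pair Bonferroni, 80% power needs a difference of about 1.3 to 1.4 SD of change. The trigger for the pairwise tests is also not the effect that was powered.

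All contrast figures rest on the assumed correlation, pattern of means and number of pairs. The documents support neither that the dose hypothesis is bound to be confirmed nor that the dose contrasts are without power in every case. This should be fixed, but it does not invalidate the design: the arms already isolate both contrasts.

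**What to change.** Name LIHV−LILV (volume) and HIHV−LIHV (intensity) as the two dose contrasts, on the 12-week value adjusted for baseline. Test them with Holm's procedure or at 0.025 each, without requiring a significant omnibus or group main effect, and report both with confidence intervals. Baseline is already collected. Adjusting for it multiplies the relevant SD by about √((1+ρ)/2) relative to change scores: 0.71 at ρ = 0 and 0.87 at ρ = 0.5.

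Keep the three training-versus-control comparisons as a separate, labelled family with its own stated alpha (Dunnett's method would suit). If both families run at 0.05, say that the combined error can reach 0.10 per outcome.

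In Sample size calculation, state that the 95% refers only to the four-arm interaction and give the correlation used. Quote the detectable difference for the dose contrasts: on change scores, 1.24 SD at 13 per arm with two contrasts at 0.025.

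The cost is analysis wording, through the amendment route the article describes. LILV versus HIHV becomes supportive, and the stated power for the dose question looks less favourable. The change does not make the trial large enough for modest dose effects: equal steps at ρ = 0 would need 62 per arm (248 in total) for 80% power at 0.025 on change scores.

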### Group allocation

Random allocation to one of the four groups will occur after confirmation of eligibility and baseline assessment. Blind allocation by a remote researcher will be performed using computer-generated random numbers. The concealment of allocation will be ensured by using sequentially numbered, sealed, and opaque envelopes.

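### Post hoc comparisons are triggered by the group main effect, although the training effect is the Group × Time interaction that the sample size was calculated for

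*Protocol article*

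**What the plan says.** Under Statistical analyses, the protocol article specifies that a "4 × 2 split-plot ANOVA with group (LILV, LIHV, HIHV, control), time (baseline, 12 weeks) and interaction effect (Group × Time) will be employed". The only follow-up rule comes next: "If the main effect of a group is found to be significant, the Bonferroni test will be employed as post hoc analysis". Nothing is said about following up a significant interaction. The level is given as "The significance level will be set at *p* < 0.05".

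Under Sample size calculation, the test used is the F test for "repeated measures analysis of variance (ANOVA), within-between interaction". The input is described thus: "An effect size of 0.44 was obtained from the data relative to changes in maximum aerobic capacity". The result is that "the total sample size required would be 52 to have 95% power at effect size of 0.44 and alpha level of 0.05", and after allowing for dropout "the total sample size obtained is 60 or 15 subjects per group, using the allocation ratio of 1 for the four groups".

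Under Group allocation: "Random allocation to one of the four groups will occur after confirmation of eligibility and baseline assessment". The Outcomes section gives two assessments, at baseline and at 12 weeks.

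**The concern.** The trial asks which training doses differ, and only the pairwise comparisons answer that. The stated way into them is an F test on arm means averaged over both visits. Half of that average was measured before anyone was randomised, so it carries no training effect. The sample size section relies on a different term of the same model, the interaction.

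Two things are at stake. A real difference in change between arms can show up in the interaction and still not meet the stated condition for pairwise testing. Conversely, a chance difference at baseline can meet that condition when training has done nothing. Even when the condition is met, comparisons of the group marginal means compare time-averaged values rather than training effects. The rule is not limited to particular outcomes, so it applies to every primary outcome in Table 2.

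**Working it through.** **Inputs from the article.** Four arms, two assessments, effect size 0.44 (taken as Cohen's f, because the scale is not stated), alpha 0.05, N=52 before dropout, 60 (15 per arm) after. **Assumed:** ρ, and the pattern of 12-week effects in step 4.

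**1. Reproduce N=52.** For the within-between interaction, λ = f²·N·m/(1−ρ) with m=2 and df = 3, N−4. At ρ=0, λ = 0.44²·52·2 = 20.13 and power is 0.964. At N=48, power is 0.948, so 52 is the smallest multiple of four that reaches 95%. Other readings do not give 52: ρ=0.5 gives 28, and f taken on the change-score scale (λ = f²·N) gives 96.

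**2. Compare the two tests.** Let the 12-week effects be d_j, with n per arm, SD σ at each visit and equal expected baselines.

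- Interaction (arms compared on change): contrast d_j, variance 2σ²(1−ρ), so λ_int = nΣ(d_j−d̄)² / [2σ²(1−ρ)].
- Group main effect (arms compared on the two-visit average): contrast d_j/2, variance σ²(1+ρ)/2, so λ_group = nΣ(d_j−d̄)² / [2σ²(1+ρ)].
- Ratio: λ_group/λ_int = (1−ρ)/(1+ρ).

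The ratio is 1 at ρ=0, 1/3 at ρ=0.5 and 1/9 at ρ=0.8.

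**3. Power of the group test at N=52, under two readings of the planned effect.** Column A holds the interaction at λ=20.13 (96% power) for every ρ, so the 12-week effect shrinks as ρ rises. Column B keeps f=0.44 on the scale that reproduces 52, so λ_group = 20.13/(1+ρ) and interaction power is 96% at ρ=0 and above 99% from ρ=0.3.

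| ρ | A: λ_group | A: power | B: λ_group | B: power |
|---|---|---|---|---|
| 0 | 20.13 | 96% | 20.13 | 96% |
| 0.3 | 10.84 | 76% | 15.49 | 90% |
| 0.5 | 6.71 | 53% | 13.42 | 85% |
| 0.7 | 3.55 | 30% | 11.84 | 80% |
| 0.8 | 2.24 | 20% | 11.19 | 78% |

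Column B is a very large effect. With f = SD(d_j)/(2σ), f=0.44 needs about 2.0 SD between control and three equally effective arms, or 2.4 SD between extreme arms with equal steps.

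**4. More moderate effects, 15 per arm.** Assume 12-week effects of 0, 0.5, 0.75 and 1.0 SD. Then d̄ = 0.5625 and Σ(d_j−d̄)² = 0.547.

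- ρ=0.5: λ_int = 15·0.547/(2·0.5) = 8.20, power 63%. λ_group = 15·0.547/(2·1.5) = 2.73, power 24%.
- ρ=0.8: λ_int = 15·0.547/(2·0.2) = 20.5, power 97%. λ_group = 15·0.547/(2·1.8) = 2.28, power 20%.

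In simulation, 76% to 81% of the trials with a significant interaction had a non-significant group effect (ρ from 0.5 to 0.9).

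**5. No training effect.** In simulation with 15 per arm, the group test is significant in about 5% of trials overall. Among trials whose arms differ at baseline by chance at p<0.05, it is significant in 49% (ρ=0.5) to 77% (ρ=0.9). About 95% of all null openings come with a non-significant interaction.

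**The case against.** The strongest reply concerns frequency. A reader might infer that real training effects will usually never be followed up. The article does not support that, because it gives no ρ and does not state the scale of 0.44. The inputs that reproduce 52 include ρ=0, and there the two tests have the same power and nothing is lost. Column A keeps a noncentrality derived at ρ=0 while raising ρ, which amounts to assuming a smaller effect. On the literal f=0.44, the group test is still significant in about 75% to 85% of trials at N=52 for ρ from 0.5 to 0.9. All of this stands, and it is why a range is shown. It does not remove the problem, because the effect in column B is very large and step 4 shows a heavy loss for effects up to 1 SD.

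A reader might also infer that the rule inflates the overall false-positive rate. It does not: the rate stays near 5%. The harm depends on a chance baseline imbalance. The planned one-way ANOVA at baseline could make such an imbalance visible, but would not change which term opens the pairwise tests.

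Finally, the rule says what happens if the group effect is significant. It does not forbid following up the interaction, and a condensed article may leave that to a fuller plan. That is fair as far as it goes. The point here is not missing detail: the one trigger that is written down is the wrong term.

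**Conclusion.** The rule is wrong as written and does not match the article's own sample size basis. For any ρ above 0 the group main effect is the weaker test of training, and at no ρ does it isolate the training effect. A real effect can therefore go without the stated follow-up, and this becomes more likely as ρ rises.

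How often depends on two quantities the article does not settle. With the interaction at its planned power, group-test power runs from 96% (ρ=0) to 20% (ρ=0.8). With the very large effect that reproduces N=52, it falls only to 78% at ρ=0.8. With assumed effects up to 1 SD and 15 per arm, the group test is significant in 20% to 24% of trials, against 63% to 97% for the interaction (ρ from 0.5 to 0.8). The ratio (1−ρ)/(1+ρ) rests on equal variances at the two visits and equal expected baselines; the second follows from randomising after baseline.

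**What to change.** Replace the post hoc sentence with one pre-specified rule, either:

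- (a) If the Group × Time interaction is significant, Bonferroni-adjusted pairwise comparisons between arms are made on the change from baseline; or
- (b) The group effect on the 12-week value adjusted for baseline (ANCOVA) is tested; if it is significant, Bonferroni-adjusted pairwise comparisons are made on the baseline-adjusted 12-week means.

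Add that the group main effect of the split-plot model is not used for inference on training.

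Option (a) matches the sample size basis. Option (b) is a different test, usually the more powerful one. With the step 4 effects and 15 per arm, simulated power was 63% for (a) and 76% for (b) at ρ=0.5, and the two disagreed on significance in 18% of trials. They are not interchangeable, so one must be chosen before the data are seen.

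The cost is one sentence and an amendment by the route under Protocol amendments (ethics committee approval and notice to the registry). N does not change. The article reports recruitment as still open and plans no interim analysis, so at that stage the change could be made before results were known.

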### Ethics

The trial methodology has been designed to incorporate features that minimize bias in controlled trials: randomization, concealed allocation, specification of eligibility criteria, blinded outcome assessment, blinded analysis, and ITT analysis.

This protocol was registered at the Clinical Trials Registry of India (CTRI/2017/08/009459) and was prospectively approved by the Institutional Ethical Committee, Jamia Millia Islamia (Reference:17/9/43/JMI/IEC/2015).

### Protocol amendments

Potential protocol modifications will be formally approved by the Institutional Ethical Committee before being implemented. The amendments will be communicated to the trial registries and outlined at the study dissemination.

## Discussion

Aerobic exercise training is an effective intervention for the prevention and treatment of insulin resistance and T2DM, but there is no unequivocal exercise prescription currently available. Investigations that have studied the effects of aerobic training in T2DM have used a spectrum of exercise volumes and intensities, but a comparison of these results in order to establish the most effective prescription remains unexplored. In addition, since the same amount of exercise training does not uniformly affect all cardiometabolic variables, a dose-response study would provide threshold dosimetry to bring about changes in the variable of interest and improve the specificity of the exercise prescription.

Oxygen kinetics and oxidative stress are highly sensitive to the magnitude of physical activity. The intensity of exercise is a significant determinant of (a) the profile of oxygen consumption influencing the presence/absence of a slow component and (b) the redox balance that impacts on the levels of oxidative stress. It would therefore be relevant to study their interaction with chronic exposure to various doses of exercise.

Another interesting facet of the study is exploring the response of NO, which might play a significant role in the regulation of oxygen uptake, oxidative stress, and cardiac autonomic function. The dual role of NO as a vasodilator and a competitive inhibitor of cytochrome-c inhibition of mitochondrial respiration, results in increased oxygen delivery but compromised utilization through the electron transport chain. This maintains high intramyocyte PO2 levels that are elevated during exercise and are speculated to affect oxygen kinetics. Superoxide reacts rapidly with NO, reducing NO bioactivity and producing the oxidative peroxynitrite radical. SOD catalyzes the conversion of superoxide to hydrogen peroxide, sparing NO. It also potentiates the exercise-induced eNOS expression through hydrogen peroxide. This suggests there is a close linear relationship between NO bioavailability and antioxidant enzymes. Paradoxically, due to its labile state, NO at high concentrations is also a source of oxidative stress. In addition, there is strong evidence for the presence of NOS distributed throughout cardiac autonomic neurons, but in studies its activity is equivocal. NO-mediated response to training is dependent on a host of factors including the levels of NOS expression and activity, severity of oxidative stress, NO binding to antioxidant molecules hemoglobin and glutathione [39], and individual patterns of physical activity [40, 41]. For these highly varied outcomes, evidence suggests the possible existence of an exercise amount/effort threshold pivotal for the regulation of NO production. However, the precise identification of these physical effort thresholds requires further study.

Exploring the optimal volume and intensity to bring about positive changes in oxygen consumption responses, oxidative status and cardiac autonomic function may hold important clinical implications and may help identify the underlying mechanisms of the differential effects of varying doses.

### Trial status

The trial is currently recruiting participants. Recruitment began in February 2016 and is anticipated to end in May 2018. The trial registration number is CTRI/2017/08/009459.

Registration date: 23 August 2017 registered retrospectively at Clinical Trials Registry - India (ctri.nic.in)

## Abbreviations

ADA: American Diabetes Association
ANOVA: Analysis of variance
BMI: Body mass index
BP: Blood pressure
CONSORT: Consolidated Standards of reporting trials
ECG: Electrocardiography
EPOC: Excess post-exercise oxygen consumption
HbA1c: Glycosylated hemoglobin
HDL-C: High-density lipoprotein cholesterol
HIHV: High-intensity, high-volume training
HPLC: High-performance liquid chromatography
HRR: Heart rate recovery
HRV: Heart rate variability
ITT: Intention to treat
LDL-C: Low-density lipoprotein cholesterol
LIHV: Low-intensity, high volume training
LILV: Low-intensity, low-volume training
MHR: Maximal heart rate
NO: Nitric oxide
ROS: Reactive oxygen species
SOD: Superoxide dismutase
SPIRIT: Standard Protocol Items: Recommendations for Interventional Trials
T2DM: Type 2 diabetes mellitus
VO_2_: Volume of oxygen consumed
VO_2_max: Maximum volume of oxygen consumed
VO_2_R: Volume of oxygen consumed at reserve
VO_2_rest: Volume of oxygen consumed at rest
VT: Ventilatory threshold
